**Patients' population:**

**ACS group:** 25 patients with an ACS diagnosed during the routine hormonal workup of an adrenal incidentaloma, who are in regular care at the Division of Endocrinology and Metabolism, Medical University of Vienna, will be included. Contact exists to > 500 patients with an adrenal incidentaloma based on recent registry analysis. Patients in routine care at the endocrine outpatients' clinic will be invited to participate in study related activities. In addition, eligible patients from the registry will be contacted by a letter, starting with the most recent ones.

**Inclusion criteria for the ACS group:**

- Age > 18 years
- History of an adrenal adenoma
- morning cortisol > 1.8 ug/dl following 1 mg dexamethasone suppression test
- No classical clinical features associated with the presence of Cushing's syndrome

**Control group:** 25 patients with an adrenal incidentaloma, in which endogenous hypercortisolism was excluded during the routine hormonal workup at the Division of Endocrinology and Metabolism, Medical University of Vienna, will be included as control group.

**Inclusion criteria for the control group:**

- Age > 18 years
- History of an adrenal adenoma
- morning cortisol of  $\leq$  1.8 ug/dl following 1 mg dexamethasone suppression testing

**General exclusion criteria:**

- HbA1c > 8 % and/or treatment with insulin therapy

- uncontrolled hypertension (RR > 170/110 mmHg; treatment with no more than 4 antihypertensive drugs)
- previous treatment with glucocorticoids within the last 3 months
- concomitant treatment with drugs affecting HPA signaling or CYP3A4 metabolism
- adrenal tumor with radiological criteria suspicious for malignancy
- chronic kidney disease (eGFR < 45 ml/min)
- liver disease (ASAT / ALAT > 3 x ULN)
- pregnancy or breast feeding
- general MR contraindications (claustrophobia, metal devices or other magnetic material in the body which will be hazardous for MR investigation)

Of note, all biochemical work-up of hormonal activity of the adrenal incidentaloma will be performed at the endocrine outpatients' clinic independently of study related activities. Only patients, who already completed their hormonal analyses will be asked to participate in the study.

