##### **Secondary outcome parameters:**

- insulin secretion and sensitivity based on validated indices (HOMA\_IR, CLIX)
- subcutaneous and visceral fat mass, body composition
- Systolic and diastolic heart function, epicardial and pericardial fat mass
- ectopic lipid deposition in the skeletal muscle and the myocardium
- standardized blood pressure measurements (blood pressure for 24h hours and Schellong tests)
- parameters of systemic inflammation (CRP, IL-6, PAI-1, TNF-alpha, homocysteine, leucocytes, monocytes)
- parameters of the Renin-Angiotensin-Aldosterone system (RAAS) activation (RAAS FINGERPRINT®) (18)

- hypercoagulability assessment by thrombin generation assays (TECHNOTHROMBIN ®)
- standardized clinical chronotype evaluation by Munich ChronoType Questionnaire and psychological testing
- body temperature measurements during the day by an actimetry watch
- analyses of peroxiredoxin oxidation cycles from red blood cells (19),
- circadian clock transcript changes from peripheral blood mononuclear cells (20),
- combined untargeted/targeted LC-MS/MS based approaches
- concentrations of testosterone and adrenal androgen precursors
- gender specific differences

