**12. Prospective benefits/relevance**

We suppose, that patients with ACS exhibit subclinical signs of 1) disturbed glucose and lipid metabolism, like impaired insulin tolerance, increased visceral fat mass and ectopic hepatic lipid deposition, as well as 2) cardiovascular risk factors, including higher blood pressure, diastolic dysfunction and increased left ventricular septal thickness, as well as 3) changes in chronobiology patterns. Medical restoration of a physiological circadian cortisol rhythm will normalize alterations in the individual chronobiology profile, accompanied by improvements in surrogate parameters of cardiometabolic risk.

Furthermore, the identification of a disease specific chronobiology pattern, which enables to identify even subtle alterations in HPA axis, might offer a novel diagnostic approach to select patients with ACS from non-functioning adrenal incidentaloma. This might help to diagnose patients at risk for adverse effects of unphysiological adrenal cortisol secretion at an early stage, before cardiometabolic and musculoskeletal sequelae develop. The results of this feasibility study might therefore pave the way for future, large interventional studies addressing this promising topic.

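### The antihypertensive-drug clause in the exclusion list runs the wrong way; separately, nothing keeps an adenoma with aldosterone excess out of either group

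*Protocol*

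**What the plan says.** Under the protocol's heading "General exclusion criteria", which covers both groups, one bullet reads "uncontrolled hypertension (RR > 170/110 mmHg; treatment with no more than 4 antihypertensive drugs". Two conditions stand inside one bracket, separated by a semicolon, and nothing says whether either is enough or both are needed. No other section restates or corrects the rule.

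On hormonal activity, the control group is described as "25 patients with an adrenal incidentaloma, in which endogenous hypercortisolism was excluded during the routine hormonal workup". Its only hormonal entry criterion is morning cortisol at or below "1.8 ug/dl following 1 mg dexamethasone suppression testing". ACS patients need a value above that cut-off and no classical Cushing features. Both groups need a history of adrenal adenoma. The one exclusion about the tumour itself is "adrenal tumor with radiological criteria suspicious for malignancy". The section adds that "Only patients, who already completed their hormonal analyses will be asked to participate in the study", but names no result of that work-up as a reason to exclude.

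The secondary outcomes include "parameters of the Renin-Angiotensin-Aldosterone system (RAAS) activation", 24-hour blood pressure, and systolic and diastolic heart function. Section 12 hopes that a chronobiology pattern "might offer a novel diagnostic approach to select patients with ACS from non-functioning adrenal incidentaloma".

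**The concern.** An exclusion for uncontrolled hypertension should remove patients whose pressure is too high or who need too much treatment. A ceiling on the number of drugs is natural as a condition for entry. Placed in an exclusion list, it removes the less intensively treated and spares the most intensively treated. The clause governs all 50 cross-sectional patients and the 15 who receive metyrapone, and the section on periodic monitoring requires full verification of adherence to the eligibility criteria. A monitor cannot verify a rule whose literal text conflicts with its own label.

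The hormonal gap is a different and smaller matter. The cross-sectional comparison is meant to show what cortisol does to cardiometabolic risk. Aldosterone belongs to the RAAS, and its excess also acts on blood pressure and the heart. A patient with that excess therefore carries an abnormal profile on several compared outcomes for a reason unrelated to cortisol.

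**Working it through.** **Part 1: the hypertension bullet.** No figure in the protocol needs reproducing here; the check is a reading of the rule. Let A be pressure above 170/110 and B be treatment with no more than 4 drugs. The bullet excludes either on A or B, or on A and B together.

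| Patient | Excluded if 'or' | Excluded if 'and' |
|---|---|---|
| At or below 170/110, up to 4 drugs | Yes | No |
| At or below 170/110, 5 or more drugs | No | No |
| Above 170/110, up to 4 drugs | Yes | Yes |
| Above 170/110, 5 or more drugs | Yes | No |

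- Under 'or', everyone above the limit is excluded, as the label implies. So is every patient at or below the limit on up to 4 drugs. The only patients left eligible are those on 5 or more drugs with pressure at or below the limit.
- Under 'and', patients above the limit are excluded only if they take up to 4 drugs. Those above the limit despite 5 or more drugs stay eligible.

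Whether a patient on no drugs counts as treated with no more than 4 is also left open. The answer moves untreated patients between cells but does not make either column fit the label.

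**Part 2: other hormone excess.** Take a patient with an adrenal adenoma, aldosterone excess and no radiological suspicion of malignancy, who meets the other general criteria.

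1. Control group: adult, history of adenoma, cortisol suppressed after dexamethasone. Eligible.
2. ACS group: the same, but cortisol not suppressed and no Cushing features. Eligible.
3. Completed work-up: satisfied once the tests are done, whatever they show on hormones other than cortisol.
4. Analysis (Statistical Analysis, Aim 1): unpaired t-tests, with regression adjustment only if age differs widely. Nothing stated there adjusts for such a patient.

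Inputs for size: 25 per group, 50 in all (Study design). One patient is 1/25 = 4% of a group. The protocol gives no share p of such adenomas among otherwise eligible patients, so p is an assumption. The expected number among 50 is 50p, and the chance of at least one is 1 − (1 − p)^50.

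| Assumed p | Expected among 50 | Chance of at least one |
|---|---|---|
| 1% | 0.5 | 39% |
| 2% | 1.0 | 64% |
| 5% | 2.5 | 92% |
| 10% | 5.0 | 99% |

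These figures show how easily one or a few such patients could enter. They do not estimate the resulting shift in any outcome, for which the protocol gives no basis.

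**The case against.** The strongest reply on the first part is that the purpose is plain. The bullet is labelled uncontrolled hypertension, and staff are unlikely to turn away untreated normotensive patients under that label; they may well read the drug count as a permitted maximum. That is fair, and it makes the harm a risk and not a certainty. It does not rescue the text, because the intended rule has to be guessed.

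A reader might go further and infer that neither reading excludes poorly controlled hypertension. The table shows otherwise: 'or' excludes everyone above the limit, and 'and' excludes those above it on up to 4 drugs. Nor is it shown that the clause selects differently in the two groups. It applies identically to both, and any pressure ceiling, correctly worded or not, would bear more on a group with higher pressure.

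On the second part, the reply is that the control group is defined consistently by cortisol, the axis under study, and that wanting fully non-functioning controls is a design preference. This largely stands. Section 12 could be taken to define the comparator as non-functioning incidentaloma, but that sentence describes a possible future diagnostic use; the comparator is defined in the Methods. A reader might also add catecholamine-secreting tumours to the list. The requirement of an adenoma weakens that example, so aldosterone excess is the case that matters. Investigators will also have the work-up results in hand, although no rule tells them to act on them.

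**Conclusion.** The hypertension exclusion is wrong as written and needs correcting. This rests on the wording alone. How many patients would be misclassified depends on how staff apply it, which the protocol does not let one judge.

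The missing exclusion for other hormone excess is an improvement worth making and not a contradiction. Its size is unknown: each patient is 4% of a group, and the number of such patients rests on an assumed share. It bears on the between-group comparison of RAAS activity, 24-hour blood pressure and cardiac function, all secondary outcomes in a study that calls itself a pilot with an exploratory analysis.

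Two further inferences are not supported. The primary outcome, hepatic lipid content, is affected only through who is enrolled, and no bias in it is shown. The metyrapone part compares patients with themselves, so between-group contamination does not apply there.

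**What to change.** 1. Split the hypertension bullet into two separate exclusions, one for the blood-pressure limit and one for the drug count, each with its direction spelled out. The sponsor must state the drug-count limit it intended and reconcile the clause with the heading it stands under.
2. Add a general exclusion for other hormone excess, chiefly aldosterone, found in the routine work-up. This also matches the contrast with non-functioning incidentaloma named in section 12.

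The cost is two lines in an eligibility amendment. No new test is needed, because the work-up is complete before patients are invited. The downside is a slightly smaller pool, drawn from more than 500 registry patients.

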**Working plan B (WPB):**

A subgroup 15 consecutive patients, who fulfill the diagnostic criteria of an ACS, will undergo a 12 weeks treatment period with metyrapone. Metyrapone will be administered with 500 mg at 6 p.m. and 250 mg at 10 p.m., which was previously shown to normalize the circadian cortisol rhythm (10) with only limited risk of an adrenal insufficiency because of the short half-life of the drug.

In these patients, all measurements of WPA will be performed at baseline and after 12 weeks of treatment with metyrapone.

A total of 125 ml blood will be drawn at study inclusion and after 12 weeks of treatment. Therefore, 250 ml blood will be drawn overall during the 3 months study period.

Additionally, to the above-mentioned measurements, the usage of an actimetry watch during the study period will help to monitor the sleep-wake cycles, temperature fluctuations and activity of the individuals to evaluate changes over time.

A clinical evaluation at the endocrine outpatients' clinic will be performed after 2, 4 and 8 weeks of treatment to assess the compliance of study drug intake and clinical tolerance, as well as the need for adaptations in concomitant treatment. Besides blood

pressure, heart rate and body weight, clinical signs of adrenal insufficiency (fatigue, orthostatic hypotension, hypoglycemia) will be recorded systematically. Blood will be drawn only in case of clinical need.

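### Metyrapone part (WPB): no stable-dose period before baseline for antihypertensive or non-insulin glucose-lowering drugs in an uncontrolled before/after comparison (minor, cheap to fix)

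*Protocol*

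**What the plan says.** The general exclusion criteria (section 5) apply to all participants and contain four drug-related rules:

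- Glucocorticoids: "previous treatment with glucocorticoids within the last 3 months". This is the only rule with a time window.
- Glucose-lowering treatment: "HbA1c > 8 % and/or treatment with insulin therapy". Non-insulin drugs are allowed, with no condition on when they were started or changed.
- Antihypertensives: "uncontrolled hypertension (RR > 170/110 mmHg; treatment with no more than 4 antihypertensive drugs". This concerns pressure level and number of drugs, not duration.
- Drugs acting on HPA signaling or CYP3A4 are barred.

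The ACS inclusion criteria, the WPB description and section 7 (Study medication) add no stable-dose rule, washout or run-in. WPB takes "A subgroup 15 consecutive patients, who fulfill the diagnostic criteria of an ACS". Clinic visits at weeks 2, 4 and 8 assess adherence and tolerance "as well as the need for adaptations in concomitant treatment", and "Blood will be drawn only in case of clinical need". Section 7 states that WPB has one open-label arm and that other medication is registered at each visit. The Statistical Analysis text (section 14) assigns paired t-tests to Aim 3. Secondary outcomes in section 4 include "standardized blood pressure measurements (blood pressure for 24h hours and Schellong tests", "parameters of the Renin-Angiotensin-Aldosterone system (RAAS) activation" and indices of insulin secretion and sensitivity.

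**The concern.** Aim 3 reads the change from baseline to week 12 as the result of lowering evening cortisol. With no concurrent control, anything else that moves an outcome over those weeks enters the same number. Antihypertensive and glucose-lowering drugs act directly on several listed outcomes. Patients come from routine care and may enter with an HbA1c up to 8% or a blood pressure up to 170/110 mmHg, so some may be having their treatment adjusted.

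Only the part of a drug's effect that develops after the baseline visit matters. If treatment was started or intensified just before baseline, that part can look like a benefit of metyrapone. If treatment was reduced, it can mask one. With 15 patients and no control arm, later analysis cannot fully separate the two.

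**Working it through.** **1. Reading check.** The general exclusion criteria, ACS inclusion criteria, WPB description and section 7 contain no stability rule for the two drug classes. A patient who started an antihypertensive the week before baseline is eligible for WPB.

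**2. The plan's own WPB figure.** Section 14 gives a control HCL of 5 ± 2.5, a level about 25% higher in ACS, and a fall of about 25% to the control level. Baseline is 5 × 1.25 = 6.25, so the expected change is 6.25 − 5 = 1.25 points. The SD of the paired change is not stated. Solving the paired t-test (two-sided 0.05, n = 15, 80% power) gives an SD of change of 1.607. With SD 2.5 at each visit, this corresponds to a within-patient correlation of 1 − 1.607²/(2 × 2.5²) = 0.79. The figure of 15 is thus attainable but cannot be confirmed. The SD of 1.607 is used below.

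**3. Assumed contamination.** None of these inputs is in the Protocol: 1 to 3 of 15 patients affected; a post-baseline drug effect of 5 to 10 mmHg systolic, or 10 to 30% of 6.25 for HCL, in each; SD of systolic change 8 to 12 mmHg.

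**4. Systolic pressure, all shifts in one direction.**
- Shift in mean change: 1/15 × 5 = 0.33 mmHg to 3/15 × 10 = 2.0 mmHg.
- 95% CI half-width: 2.145 × 8/√15 = 4.43 to 2.145 × 12/√15 = 6.65 mmHg.
- Ratio: 0.33/6.65 = 5% to 2.0/4.43 = 45%.
- Rejection rate with no metyrapone effect: 4.9 to 10.0% if every shift is favourable; 4.9 to 5.1% if direction is random.

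**5. HCL.**
- Shift in mean change, one direction: 1/15 × 0.10 × 6.25 = 0.042 to 3/15 × 0.30 × 6.25 = 0.375 points. Relative to 1.25 this is 3 to 30%.
- Rejection rate with no metyrapone effect, all shifts favourable (200,000 simulated trials per cell):

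| Patients affected | 10% | 20% | 30% |
|---|---|---|---|
| 1 | 5.0% | 5.1% | 5.0% |
| 2 | 5.1% | 5.8% | 6.4% |
| 3 | 5.6% | 7.3% | 9.5% |

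With random direction, all nine cells lie at 4.9 to 5.0%.

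- Power for a true effect of 1.25 (80% without contamination):

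| Patients, size | All unfavourable | Random direction |
|---|---|---|
| 1, 10% | 77.1% | 79.6% |
| 2, 20% | 65.5% | 76.8% |
| 3, 30% | 41.8% | 70.0% |

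**6. Room to recruit.** The registry holds more than 500 incidentaloma patients. With the one-third share in section 1, 500 × 1/3 = 167 would have cortisol dysregulation, and 15/167 = 9%. This is before other exclusions, consent and overlap with the 25 ACS patients needed for WPA.

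**The case against.** The glucocorticoid window is correct in itself and contradicts nothing, so this is an omission and close to a design preference. Nothing in the Protocol shows that recent drug changes are common, and every magnitude input is assumed. The upper inputs are high, because the whole shift must arise after baseline. Medication is registered at each visit, insulin and poor control are excluded, and the study calls itself a pilot with exploratory analyses. A window also leaves the main limit of WPB, the missing control arm, untouched.

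Most of this stands and sets the weight of the point. It does not remove it. Registering medication permits description but prevents nothing, and an entry criterion belongs in the protocol and cannot be supplied by an analysis plan.

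The documents do not support four stronger readings:

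- *The HCL result of WPB would be a likely false positive.* The rejection rate stays near 5% with random direction. It exceeds 7.3% in one cell of nine even if all shifts are favourable.
- *Power could fall to 42%.* That needs three patients, each with 30% of baseline HCL, all shifted unfavourably. With random direction it is about 70%.
- *Adapting treatment during the 12 weeks is a fault.* The WPB text places it among tolerance and safety checks. It is legitimate and may more often hide a benefit than create one.
- *Lipid-lowering drugs are equally central.* No serum lipid outcome is listed. They matter at most through CRP and HCL.

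**Conclusion.** The point holds as a minor improvement for WPB only. As written, the criteria admit patients whose antihypertensive or non-insulin glucose-lowering treatment has just changed, and the paired analysis counts the effect that develops afterwards as part of the metyrapone change. The exposed results are mainly exploratory secondary outcomes: 24-hour blood pressure, RAAS activation and insulin indices. HCL is probably affected only modestly. The WPA comparison, for which section 14 states the hypotheses, is not affected.

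Neither size nor direction can be derived from the Protocol, and the figures above only illustrate a range under the stated assumptions. That the gap exists follows from the text alone. Confidence that it would matter in practice is moderate at best.

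**What to change.** Add to the general exclusion criteria, for WPB: antihypertensive and glucose-lowering treatment unchanged for 3 months before the baseline visit; otherwise the baseline visit is postponed. Three months mirrors the glucocorticoid window. The investigators may prefer another length by drug class. Lipid-lowering drugs may be added, as a secondary matter.

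Changes during the 12 weeks stay allowed for clinical need. Their number and direction can be reported from the medication already registered at each visit.

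The cost is one eligibility line, with no extra visit, blood draw or MR examination. Some patients start later, and the series of 15 consecutive patients is slightly narrowed. Fifteen from roughly 167 makes this likely to be feasible, but the Protocol does not say how many patients are on stable treatment. The window does not remove regression to the mean or lifestyle change, so the report should still describe the WPB change as uncontrolled.

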## **5. Methods:**

### **Study design:**

#### **Working plan A (WPA):**

#### **Cardiometabolic phenotyping:**

To address aim 1 we will perform a cross-sectional study in patients, who are in routine care at the endocrine outpatients' clinic for the hormonal work up of an adrenal adenoma. 25 patients with an ACS will be recruited and compared to 25 patients of comparable age and sex with a sufficient suppression of cortisol  $< 1.8$  ug/dl following a 1 mg dexamethasone suppression test.

Experiments will be performed in the morning after an overnight fast. Subjects have to avoid intense physical exercise and consumption of alcoholic beverages for at least 48 hours previous to study related experiments.

$^1\text{H}$  magnetic resonance (MR) spectroscopy measurements will be performed in high field 3T whole body MR system (Magnetom, Siemens Healthcare, Erlangen, Germany) equipped with appropriate surface coils. Ectopic fat in the liver, the skeletal muscle and the myocardium will be assessed by the single voxel localized  $^1\text{H}$  MRS method (41).

After the MR measurements a frequently sampled oral glucose tolerance test will be performed and surrogate parameters of insulin secretion and sensitivity will be

calculated based on validated indices (HOMA\_IR, CLIX, OGIS, IGI, Disposition Index, Adaptation Index) (21).

Additionally, blood will be drawn at baseline for the measurement of parameters of systemic inflammation (CRP, IL-6, PAI-1, TNF-alpha, homocysteine, leucocytes, monocytes), the renin-angiotensin-aldosterone system (RAAS FINGERPRINT ®) and hypercoagulability (TECHNOTHROMBIN ®).

To estimate diurnal cycles of cortisol secretion salivary cortisol will be drawn at 8:00 a.m. and midnight.

To address aim 2, additional blood will be drawn to analyze the peroxiredoxin oxidation cycles from red blood cells (19), as well as the circadian clock transcript changes from peripheral blood mononuclear cells (21).

In addition, blood will be stored for combined untargeted/targeted LC-MS/MS based metabolomic/proteomic approaches.

Overall, 125 ml blood will be drawn in total for all biochemical analyses of WPA.

A systematical assessment of the chronotype will be performed by using the Munich ChronoType Questionnaire. Furthermore, the following psychological tests will be applied:

- Measurement of vigilant attention and impulsivity (by means of the Psychomotor Vigilance Task)
- Implicit association of concepts (by the Implicit Association Test)

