### **Statistical Analysis:**

Data will be presented as means  $\pm$  SD or median (minimum; maximum) depending on normal distribution. Normal distribution will be checked by data visualization and the Kolmogorov-Smirnov test.

Due to the exploratory design of the study, there will be no correction for multiple testing. Due to the exploratory design of the study, there will be no correction for multiple testing.

Hepatic lipid content (HCL) will be considered as primary outcome parameter.

Nullhypothesis: There is no difference in HCL between patients with ACS and the control group.

Alternative hypothesis: There is a difference in HCL between patients with ACS and the control group.

Aim 1: comparisons between the groups of patients with ACS and the control group without ACS will be performed by unpaired student's t-tests. In case of a large distribution of age between the groups, an adjustment by a regression model will be performed.

Aim 2: Comparisons of metric variables between the groups of patients will be performed by unpaired student's t-tests or Mann-Whitney-U tests, depending on normal distribution. Chi-squared test will be used for comparison of discrete variables.

Aim 3: longitudinal analysis before and after treatment will be performed by using paired student's t-tests.

Associations between continuous variables will be described by Pearson's correlation coefficient.

SPSS - Statistics will be used for all computations. Level of statistical significance is set at  $p < 0.05$ .

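### RAAS-acting drugs, anticoagulants and non-insulin glucose-lowering drugs are neither excluded nor used in the analysis, so the RAAS, thrombin-generation and insulin-index contrasts between ACS and controls may be mixed with drug effects

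*Protocol*

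**What the plan says.** **Eligibility (Protocol, section 5, General exclusion criteria).** The drug-related exclusions are:
- "HbA1c > 8 % and/or treatment with insulin therapy";
- glucocorticoids within the last three months;
- "concomitant treatment with drugs affecting HPA signaling or CYP3A4 metabolism".

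Antihypertensives appear only within "uncontrolled hypertension (RR > 170/110 mmHg; treatment with no more than 4 antihypertensive drugs". In a list of exclusions that phrase is ambiguous and the sponsor should reconcile it, but no class is singled out. Anticoagulants and non-insulin glucose-lowering drugs are not mentioned.

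**Design (section 5, Cardiometabolic phenotyping).** "25 patients with an ACS will be recruited and compared to 25 patients of comparable age and sex". The conditions before testing cover fasting, exercise and alcohol, not drugs.

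**Outcomes (section 4, secondary).** "parameters of the Renin-Angiotensin-Aldosterone system (RAAS) activation", "hypercoagulability assessment by thrombin generation assays" and "insulin secretion and sensitivity based on validated indices".

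**Analysis (section 14, Statistical Analysis).** For Aim 1, "comparisons between the groups of patients with ACS and the control group without ACS will be performed by unpaired student's t-tests". The only covariate named is age, to be used if the groups' ages differ widely.

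**Recording (section 7).** Concomitant medication is noted at every visit. No stated analysis uses it.

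**The concern.** Each of these drug classes acts on the system that one of the assays measures: RAAS-acting drugs on the RAAS profile, anticoagulants on thrombin generation, glucose-lowering drugs on HOMA_IR and CLIX. Followed as written, the analysis compares the groups with these effects left in.

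The consequences differ by outcome:
- **RAAS.** If more ACS patients than controls take RAAS-acting drugs, or fewer, the t-test can show a group difference with no cortisol effect behind it.
- **Thrombin generation.** An anticoagulated patient gives a low value for a drug reason. This inflates the variance whichever group the patient is in. In the ACS group it also pulls the mean against the hypothesised hypercoagulability. The main risk is a missed difference.
- **Insulin indices.** If glucose-lowering drugs are commoner in ACS, treatment would be expected to narrow a real difference.

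Aim 1 sets out to describe these risk factors in ACS, and section 12 hopes that the results will prepare larger trials. A RAAS or coagulation result that cannot be separated from prescribing serves that purpose poorly.

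**Working it through.** The protocol gives no prescribing rates, drug effects or expected values for these outcomes, so there is no figure of its own to reproduce. What follows is illustration. From the protocol: 25 per group, unpaired t-test, significance level 0.05, taken as two-sided because the alternative hypothesis is a difference. Everything else is assumed.

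**RAAS marker, no true ACS effect.** A fraction pA of ACS patients and pC of controls take a drug that shifts a log-scale marker by g SD.
- Apparent difference: D = (pA − pC) × g
- Pooled SD: S = √(1 + g² × [pA(1 − pA) + pC(1 − pC)]/2)
- Non-centrality: (D/S) × √(25/2) = 3.536 × D/S, with 48 degrees of freedom

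| Use, ACS v control | g | D | S | D/S | Non-centrality | Rejection rate |
|---|---|---|---|---|---|---|
| 60% v 30% | 1 | 0.30 | 1.107 | 0.271 | 0.958 | 15.6% |
| 60% v 30% | 2 | 0.60 | 1.378 | 0.435 | 1.539 | 32.6% |
| 50% v 30% | 1 | 0.20 | 1.109 | 0.180 | 0.638 | 9.6% |
| 50% v 30% | 2 | 0.40 | 1.386 | 0.289 | 1.021 | 17.0% |
| 50% v 40% | 1 | 0.10 | 1.116 | 0.090 | 0.317 | 6.1% |
| 50% v 40% | 2 | 0.20 | 1.407 | 0.142 | 0.503 | 7.8% |
| equal use | any | 0 | – | 0 | 0 | 5% |

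Simulation (20,000 replicates) agrees to within about one percentage point. The result depends almost wholly on the imbalance.

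**Thrombin generation, true effect present.** Assumed: controls mean 100, ACS mean 120, SD 20 in both. With nobody anticoagulated the standardised difference is 20/20 = 1 and power is about 94%. Now replace some values by anticoagulated ones around 20 (SD 5).
- One in ACS: the ACS mean falls by 100/25 = 4, so the difference is 16. The ACS variance becomes 0.96 × 400 + 0.04 × 25 + 0.04 × 0.96 × 100² = 769. Pooled SD = √((769 + 400)/2) = 24.2. Standardised difference = 16/24.2 = 0.66.
- Two in ACS: the difference is 12. ACS variance = 0.92 × 400 + 0.08 × 25 + 0.08 × 0.92 × 100² = 1,106. Pooled SD = √((1,106 + 400)/2) = 27.4. Standardised difference = 0.44.
- One in each group: the means are 116 and 100 − 80/25 = 96.8, difference 19.2. Control variance = 385 + 0.04 × 0.96 × 80² = 631. Pooled SD = √((769 + 631)/2) = 26.5. Standardised difference = 0.73. Balance protects the mean difference but not the variance.

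Simulated power of the t-test:

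| Anticoagulated patients | Value near 20 | Value near 60 |
|---|---|---|
| none | 94% | 94% |
| one, ACS only | 65% | 83% |
| two, ACS only | 24% | 66% |
| one in each group | 76% | not tabulated |
| two in each group | 53% | not tabulated |

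A weaker drug effect spread over both groups would cost less than the mildest row shown. In the balanced scenarios, leaving these patients out of this one analysis brings power back to about 91% to 93%.

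**Insulin indices.** No calculation was made. The argument there is about direction only.

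**The case against.** Five points on the other side carry weight.

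1. **This could sit in a SAP.** One may exist, and the statistical section does not say that age is the only covariate permitted. That is fair for detail. But the protocol itself fixes the test, names one covariate, sets eligibility and sets the conditions before sampling, so the comment concerns what is written.

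2. **Imbalance is not established.** A reader might infer that drug use is bound to differ, because section 12 expects higher blood pressure and disturbed glucose metabolism in ACS. That section calls these signs subclinical, which does not establish more prescribing. Controls are adenoma patients from the same clinic, of comparable age and sex, under the same exclusions. Nothing suggests more anticoagulant use in ACS. This stands: imbalance is plausible, not shown.

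3. **The drugs need not dominate.** A reader might infer that these drugs determine the outcomes, or that any group difference would be a prescribing effect. The documents give no drug effect sizes. Only the RAAS scenario creates a spurious difference; the other two mainly hide a real one. A value of 20 is also (120 − 20)/20 = 5 SDs below the assumed ACS mean and would show up in the planned data plots, but the plan does not say what would then be done for Aim 1.

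4. **Adjustment may be wrong.** If hypertension or dysglycaemia results from cortisol excess, drug use lies downstream of ACS. Adjusting for it can remove part of the effect sought, and untreated patients may be milder cases. This stands, and it argues against an adjusted comparison as the main analysis.

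5. **Limited reach.** These are secondary outcomes in an exploratory pilot. Nothing here bears on liver fat, the primary outcome, and the medication data will exist in any case.

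**Conclusion.** The gap is in the text: these drug classes are not excluded, no rule before sampling deals with them, and the stated comparison makes no use of the medication record. What follows from it is conditional.

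- **RAAS:** the contrast can partly reflect prescribing if use differs between groups. With a 1 to 2 SD drug shift, the false-positive rate is 6% to 8% at 50% v 40% use and about 16% to 33% at 60% v 30%. With equal use it stays at 5%.
- **Thrombin generation:** this does not need imbalance. One or two anticoagulated patients, in the ACS group or in each group, take power from about 94% to between 24% and 83% in the scenarios run.
- **HOMA_IR and CLIX:** masking is possible if glucose-lowering drugs are commoner in ACS. Its size was not estimated.

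All these sizes rest on assumed prescribing rates, drug effects and assay values; the true size is unknown. The point justifies a cheap addition to the analysis, not a claim that the Aim 1 results would be invalid.

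**What to change.** Add one paragraph to the Statistical Analysis section:

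1. **Thrombin generation.** Leave patients on therapeutic anticoagulation out of this analysis only, and report how many there were in each group.
2. **RAAS and insulin outcomes.** Tabulate the use of RAAS-acting drugs (by class) and of glucose-lowering drugs by group, and keep the unadjusted comparison. Add pre-stated sensitivity analyses: the RAAS FINGERPRINT by RAAS-drug use, with the untreated subset shown, and HOMA_IR and CLIX in patients without glucose-lowering drugs.
3. **Reading the results.** State that drug use may be a consequence of cortisol excess and that untreated patients may be milder cases, so that a smaller difference in the subset does not by itself refute an ACS effect.

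The cost is slightly fewer patients for thrombin generation and wider intervals in the subsets. The medication data are already to be collected. No patient's treatment or eligibility changes, and nobody leaves the primary liver-fat analysis.
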